### Surgical Procedure and Multimodal Analgesia Plan

2.5

Patients will undergo primary unilateral TKA with insertion of a non‐cruciate retaining standard cemented prosthesis by a parapatellar medial approach, without the use of a tourniquet or local infiltration analgesia [11].

All patients will receive tablets of paracetamol 1 g and ibuprofen 400 mg 1 h before surgery. Spinal anesthesia is performed with 3 mL of ropivacaine 5 mg/mL. Intravenous dexamethasone 12 mg will be administered perioperatively. Standard treatment with fluids and mild sedation using propofol will be provided at the discretion of the anesthetist. Postoperatively, tablets of paracetamol 1 g are administered four times a day and ibuprofen 400 mg three times a day. After discharge from the post‐anesthesia care unit, the patient will be provided with morphine tablets for self‐administration. The tablets allow the patients to take 5 mg morphine at a time, with a maximum oral dose of 100 mg within the first 24 h after end‐of‐surgery time. If needed, hospital staff can administer rescue doses of intravenous morphine, which will be recorded in the patient file.

### Peripheral Nerve Block Procedure

2.6

Four 10‐mL syringes are prepared with bupivacaine 5 mg/mL from the department's standard stock and brought to the nerve block procedure. Upon the patient's arrival in the post‐anesthesia care unit after surgery, the anesthesiologist will perform a femoral triangle block using 15 mL of bupivacaine. Subsequently, digital randomization will be conducted in REDCap, followed by administration of the PPB with either 10 or 20 mL of bupivacaine. Any remaining bupivacaine is discarded along with the needle to ensure that the administered volume remains blinded to the patient and clinical staff.

A 22‐gauge, 80‐mm block needle (Temena, Felsberg, Germany) is used for the procedure, guided by a Sonosite X‐Porte ultrasound system (Sonosite; Bothell, WA, USA). For the PPB, a 5–2 MHz curved array transducer (C 60xp; Sonosite) is used, whereas a high‐frequency 15–6 MHz linear array transducer (HFL 50; Sonosite) is used for the femoral triangle block.

#### The PPB Technique

2.6.1

The superficial femoral artery is identified in the adductor canal and traced caudally until it deviates from the sartorius muscle and is positioned adjacent to the posteromedial margin of the vastus medialis muscle, close to the adductor hiatus. The anatomical landmark for this position is typically 2‐5 cm cranially to the base of patellae. The needle will be inserted medially to the transducer and advanced with an in‐plane technique to the endpoint of injection located on top of the superficial femoral artery, posteromedial to the fascia of the vastus medialis muscle. We will inject the allocated volume of bupivacaine, ensuring anterolaterally spread to the artery [5].

#### The Femoral Triangle Block Technique

2.6.2

From the apex of the femoral triangle, we trace the superficial femoral artery cranially until the saphenous nerve and nerve to vastus medialis are visualized lateral to the femoral artery, and the intermediate femoral cutaneous nerve (IFCN) is visualized superficial to the sartorius muscle. This optimal ultrasonographical image is typically found 5–10 cm distal to the inguinal crease. The needle will be inserted lateral to the transducer and advanced in‐plane, piercing the sartorius muscle to the endpoint of injection lateral to the femoral artery. Here, we will inject 10 mL of bupivacaine, allowing for repositioning of the needle tip to ensure a spread around both the saphenous nerve and nerve to vastus medialis. Then, the needle tip will be retracted to the superficial side of the sartorius muscle and repositioned to inject 5 mL of bupivacaine into the “flat fat‐filled tunnel” surrounding the IFCN [12].

### Sample Size

2.7

The sample size was calculated using an online calculator (Georgiev G.Z., “Sample Size Calculator,” https://www.gigacalculator.com/calculators/power‐sample‐size‐calculator.php).

The calculation was based on the mean 24‐h opioid consumption of 33.6‐mg oral MME with a standard deviation of 31.8, as found in our previous trial using a PPB with 10 mL after TKA [5]. A superiority design with a one‐sided hypothesis test, no superiority margin, *α* = 0.05, 1−*β* = 0.8, and a minimal detectable effect of 15‐mg oral MME indicated that 56 patients per group were required. Sixty patients per group will be included to account for dropouts and potential variability.

### Study Period, Data Collection, and Analyses

2.8

The study period begins on the day of surgery, after signing the informed consent form prior to the surgery. The study period ends 24 h after the end‐of‐surgery time (=*T*
_24_). The length of the patient's hospitalization during the study period is determined by their agreement with the surgeon. Patients are allowed to be discharged during the study period.

Pain intensity will be assessed using the 11‐point Numeric Rating Scale (NRS) ranging from 0 = *no pain* to 10 = *worst imaginable pain*. Preoperative baseline pain intensity at rest and during a 10‐m walk will be obtained on the day of surgery.

Prior to assessment of postoperative walking ability with crutches, muscle function is evaluated using the MMT for dorsiflexion and plantarflexion of the ankle, as well as knee extension. MMT results will be graded from 5 to 0 [13]:

5 = active motion against gravity with maximum resistance from assessor.

4 = active motion against gravity with moderate resistance from assessor.

3 = active motion against gravity without resistance.

2 = active motion with gravity eliminated or minimal assistance from assessor.

1 = no active motion, but palpable or observable muscle contraction.

0 = no active motion or muscle contraction.

At *T*
_24_, patients will be sent an automated text message including a survey link. In the survey, patients will report their intake of the dispensed morphine tablets, pain intensity at rest and during a 10‐m walk with crutches, and complete the Quality of Recovery‐15 questionnaire [14]. Total opioid consumption will be reported as oral MME, combining hospital‐administered opioid doses from the patient file and self‐reported intake of dispensed morphine tablets.

Total opioid consumption and Quality of Recovery‐15 will be assessed with histograms and Q–Q plots and analyzed using *t*‐tests or Mann–Whitney *U* tests. Pain intensity will be analyzed with repeated measures ANOVA or linear mixed‐effects models. Differences in frequencies will be analyzed using chi‐squared or Fisher's exact tests, as appropriate. An alpha level of 0.05 is used to determine statistical significance. We predefine the minimal clinically relevant difference between the groups in the total opioid consumption as 15 mg of oral MME [15]. Analyses will follow the intention‐to‐treat principle. Missing data will not be imputed or included in the analyses, but the frequency and reasons will be reported in the article. Any changes to the statistical plan will be reported, with the final detailed plan included in the publication.

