### Inclusion and Exclusion Criteria

2.2

Patients eligible for inclusion are adults over 18 years scheduled for primary TKA under spinal anesthesia, able to provide written informed consent, and classified as American Society of Anaesthesiologists physical status 1, 2, or 3. Exclusion criteria are inability to read or speak Danish, lack of access to a smartphone with internet, allergies to study medications, preoperative consistent daily opioid intake, reliance on walking aids, substance abuse, BMI over 40, or a diagnosis of neurodegenerative disorders.

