### Outcomes

2.4

The primary outcome is total opioid consumption from *T*
_0_ (end‐of‐surgery time) to *T*
_24_ (24 h after *T*
_0_), expressed in oral morphine milligram equivalents (MME).

Secondary outcomes include:
The frequency of patients with opioid‐free analgesia from *T*
_0_ to *T*
_24_.Pain at rest at *T*
_6_ (6 ± 1 h after *T*
_0_) and at *T*
_24_.Pain during a 10‐m walk with crutches at *T*
_6_ and *T*
_24_.The frequency of patients unable to walk 10 m with crutches at *T*
_6_.The frequency of manual muscle test (MMT) < Grade 3 for dorsiflexion and plantarflexion of the ankle and knee extension at *T*
_6_.Patient‐reported quality of recovery (Quality of Recovery‐15) at *T*
_24_.

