At our hospital's elective surgery center, hospitalization is recommended only for patients without a caregiver at home or those with significant comorbidities. Additionally, patients undergoing surgery in the afternoon may not meet discharge criteria until late in the evening and are often offered overnight hospitalization for comfort, with discharge the following day. As a result, approximately one‐third of our TKA patients are discharged on the day of surgery. To ensure comprehensive inclusion, we enroll both hospitalized patients and outpatients. We do not plan any subgroup analysis between the two groups, as we believe they will be similar.

A potential limitation of this trial is the accuracy of opioid consumption recording, which could be improved using intravenous opioids via a patient‐controlled analgesia pump. However, this would require additional resources and hospitalization of all participants. Instead, we opted for a study design that aligns with our everyday clinical practice.

We hope these results will provide a clinical recommendation for the optimal analgesic volume for PPB, which can optimize postoperative pain management after TKA.

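### The total opioid outcome counts only hospital doses and the trial's own tablets, so any other opioid taken at home scores zero; one survey item would close the gap

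*Protocol article*

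**What the plan says.** Section 2.4 (Outcomes) of the protocol article states: "The primary outcome is total opioid consumption from" the end of surgery to 24 hours later, in oral morphine milligram equivalents (MME). It does not limit the opioid by source. The first secondary outcome covers the same window: "The frequency of patients with opioid‐free analgesia from" end of surgery to 24 hours. No separate data source is given for it.

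Section 2.8 then fixes how the total is formed: "combining hospital‐administered opioid doses from the patient file and self‐reported intake of dispensed morphine tablets". The only opioid item it lists for the 24-hour text-message survey is this: "In the survey, patients will report their intake of the dispensed morphine tablets".

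Three further statements bear on the point:

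- Section 2.8: "Patients are allowed to be discharged during the study period".
- Discussion: approximately one-third "of our TKA patients are discharged on the day of surgery".
- Section 2.2: on opioid use, the exclusion is "preoperative consistent daily opioid intake", so people who use opioids only occasionally remain eligible.

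**The concern.** The counting rule is narrower than the outcome it is meant to measure. A patient at home may take an opioid from a private supply or one obtained after discharge. That opioid is in neither the patient file nor the tablet count, so it enters the total as 0 MME. If the patient took no trial tablet and received no hospital opioid, the same rule classes the patient as opioid-free.

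If such use depends on pain, and the two volumes differ in analgesia, more opioid would go unrecorded in the arm with worse analgesia. The recorded difference would then be smaller than the true one. The yes/no outcome is sensitive in another way: a single uncounted dose can change a patient's class.

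**Working it through.** **Text against text.** Section 2.4 promises total consumption. Section 2.8 sums two named sources. No section asks about another opioid, forbids it, or captures it in some other way. The gap therefore follows from a stated rule and does not depend on a detail being left out.

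**Exposure.** If the Discussion's one-third applies to the trial, 120 / 3 = 40 patients, or about 20 per arm, go home on the day of surgery. Some patients who stay overnight may also be home before 24 hours.

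**The plan's own figure.** Inputs from section 2.7: SD 31.8 mg, difference 15 mg, one-sided alpha 0.05, power 0.80, 1:1 allocation. With the normal approximation:

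n per arm = 2 × (1.645 + 0.842)² × (31.8 / 15)² = 2 × 6.18 × 4.49 ≈ 55.6, rounded up to 56.

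This reproduces the stated 56. With the planned 60 per arm, the standard error of the difference is 31.8 × √(2/60) = 5.81 mg, and power is Φ(15 / 5.81 − 1.645) = 0.826.

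**Sensitivity.** The documents give no rate of other opioid use, so every rate and amount below is an assumption.

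Recorded difference = 15 − (share in 10 mL arm − share in 20 mL arm) × MME per user. The SD is held at 31.8, with 60 per arm and a one-sided test.

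| Share, 10 mL vs 20 mL | MME per user | Shrinkage | Recorded difference | Power |
|---|---|---|---|---|
| 5% vs 5% | 20 | 0 | 15.0 mg | 0.83 |
| 5% vs 2.5% | 20 | 0.025 × 20 = 0.5 mg | 14.5 mg | 0.80 |
| 10% vs 5% | 30 | 0.05 × 30 = 1.5 mg | 13.5 mg | 0.75 |
| 15% vs 7.5% | 30 | 0.075 × 30 = 2.25 mg | 12.75 mg | 0.71 |

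In the first row each arm's mean falls by 0.05 × 20 = 1.0 mg and the difference is untouched. The last row is a ceiling: 15% of 60 is 9 patients, nearly half of the roughly 20 per arm expected home on the day of surgery.

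**Opioid-free outcome.** Each misclassified patient moves an arm's proportion by 1/60 = 1.7 percentage points. Misclassification needs three things in the same patient: no hospital opioid, no trial tablet, and some other opioid.

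**The case against.** The strongest reply is that nothing in the documents shows such use occurs. Consistent daily users and people with substance abuse are excluded. Every patient is given morphine tablets that are counted, up to 100 mg orally in the window. That is about three times the planning mean (100 / 33.6 = 2.98) and 2.1 SD above it ((100 − 33.6) / 31.8). A patient in pain would ordinarily use those tablets first. Patients and assessors are blinded, so use should differ between arms only if analgesia does. The Discussion already concedes that opioid recording is imperfect, and an article may condense the list of survey items.

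Most of this stands, and it limits the weight of the point. It does not remove the point. The two-source rule is stated outright. The conceded limitation concerns recording accuracy in general and does not mention other opioids. The reason given there for not using a patient-controlled pump (resources, and hospitalization of all participants) does not apply to one more survey question.

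Two stronger readings are tempting, and the documents support neither:

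- A reader might infer that the opioid-free proportion is wrong by the full share of assumed users. That would require every one of them to have taken no counted opioid at all. This fits badly with the idea that they are the patients in most pain, who also hold counted morphine.
- A reader might also fault the survey for not asking about the scheduled paracetamol and ibuprofen. The article says nothing wrong or contradictory there, and such survey detail commonly sits in the full protocol.

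**Conclusion.** The point holds as a mismatch between a broadly defined outcome and a narrower counting rule. It is a minor issue and a cheap improvement. It affects the primary outcome and the first secondary outcome, and it changes no stated figure: 56 per arm reproduces.

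The likely effect is small. Equal use in both arms does not alter the mean difference. Heavier use in the arm with worse analgesia shrinks it by about 0.5 to 2 mg of 15 mg. That range rests entirely on assumed rates, an assumed 2:1 imbalance between arms, assumed amounts per user and an unchanged SD. A reader might infer that the primary comparison is seriously biased. The documents do not support that, because they give no evidence that such use is frequent or differs between arms. If the two volumes are equally effective, the mechanism gives no reason for use to differ, so it would not be expected to produce a false difference.

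**What to change.** Make three small changes:

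1. Add one item to the 24-hour survey already planned, asking whether any other opioid was taken since surgery and, if so, its name, strength and number.
2. In section 2.8, define total consumption as hospital doses plus dispensed tablets plus any other opioid, all in oral MME.
3. Define opioid-free as zero from all three sources.

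If the sponsor prefers not to change the survey, both outcomes should be labelled as covering hospital-administered plus dispensed opioid only.

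The cost is a slightly longer survey and a sentence or two in the outcome definitions, with no extra staff or visits. The item needs to be in the survey when it is sent, since this information cannot be recovered reliably afterwards.

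### Baseline pain is collected, but the stated primary tests cannot use it and the pain analysis gives it no role; the permitted repeated-measures ANOVA would also drop patients seen at only one time point

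*Protocol article*

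**What the plan says.** All the analysis text is in section 2.8 (Study Period, Data Collection, and Analyses) of the protocol article.

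- **Baseline data:** "Preoperative baseline pain intensity at rest and during a 10‐m walk will be obtained on the day of surgery".
- **Primary outcome:** 24-h opioid consumption in oral MME is compared by a t-test or a Mann–Whitney U test after inspection of histograms and Q–Q plots.
- **Pain:** "Pain intensity will be analyzed with repeated measures ANOVA or linear" mixed-effects models. The sentence names no covariate and no rule for choosing between the two. Section 2.4 (Outcomes) defines the pain outcomes at T6 and T24 only.
- **Missing data and analysis set:** "Missing data will not be imputed or included in the analyses, but the frequency and reasons will be reported in the article", and "Analyses will follow the intention‐to‐treat principle".
- **Where gaps may arise:** at T24, "patients will be sent an automated text message including a survey link", so that score depends on a reply. Section 2.4 also counts as an outcome "The frequency of patients unable to walk 10 m with crutches at" T6, and such patients have no T6 walking-pain score.

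Section 2.8 adds that a final detailed statistical plan will accompany the publication.

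**The concern.** There are two separate issues.

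First, a baseline value that predicts the outcome can narrow the confidence interval and correct for chance imbalance. For opioid use, the named tests rule this out. For pain, either model could include baseline, but the text does not say that it will.

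Second, the two permitted pain models treat incomplete patients differently. A classical repeated-measures ANOVA needs a complete row, so a patient with no T6 walking score also loses a valid T24 score. A mixed model keeps the observed score. With no selection rule, the set of patients analysed depends on a choice still open when the data arrive, which sits badly with the intention-to-treat statement.

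Precision is at stake for the primary outcome and the pain outcomes. For walking pain there is also possible bias, because T6 scores can be missing for a reason tied to the patient's condition.

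**Working it through.** **Step 1: the plan's own figure.** Section 2.7 uses SD 31.8, difference 15 mg, one-sided α 0.05 and power 0.80. Then n = 2 × 31.8² × (1.645 + 0.842)² / 15² ≈ 55.6, so 56 per group, as stated. This sizing is for an unadjusted comparison of mean opioid use. The article gives no SD, correlation or power for pain.

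**Step 2: what baseline adjustment can gain.** Let r be the correlation between baseline pain and the outcome. The documents do not give it, so the values below are assumed. Residual variance is multiplied by 1 − r², the standard error by √(1 − r²), and 120 adjusted patients are worth 120/(1 − r²) unadjusted ones.

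| Assumed r | 1 − r² | Fall in variance | Fall in SE | Equivalent total |
|---|---|---|---|---|
| 0.1 | 0.99 | 1% | 0.5% | 121 |
| 0.2 | 0.96 | 4% | 2.0% | 125 |
| 0.3 | 0.91 | 9% | 4.6% | 132 |
| 0.5 | 0.75 | 25% | 13.4% | 160 |

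This ignores the one degree of freedom that each covariate costs.

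**Step 3: what the ANOVA option can lose.** Assume 60 per arm, a fraction m missing independently at each of T6 and T24, unit variance, known covariance, and correlation ρ between the two times.

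- Complete patients per arm: 60 × (1 − m)². This is 60 × 0.9025 ≈ 54 at m = 5%, and 60 × 0.81 ≈ 49 at m = 10%.
- Patients per arm with exactly one score: 60 × 2m(1 − m). This is 5.7 at m = 5% and 10.8 at m = 10%. The ANOVA drops them and the mixed model keeps them.
- Worked case, m = 10% and ρ = 0.5. The inverse covariance matrix has 1.333 on the diagonal and −0.667 off it. Information per patient randomised is 0.81 × 1.333 + 0.09 = 1.17 on the diagonal and 0.81 × (−0.667) = −0.54 off it. The mixed-model variance at one time point is proportional to 1.17/(1.17² − 0.54²) = 1.086, against 1/0.81 = 1.235 for complete cases. The ratio is 0.88, so the SE falls by 1 − √0.88 ≈ 6.2%.

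| Missing at each time | Complete per arm | Fall in SE at one time (ρ 0.3 to 0.7) | Fall in SE for the mean of both times |
|---|---|---|---|
| 5% | 54 of 60 | 2.7% to 3.7% | 3.3% to 4.2% |
| 10% | 49 of 60 | 5.5% to 7.3% | 6.5% to 8.3% |

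**Step 4: distribution of the primary outcome.** The planning mean is 33.6 and the SD 31.8. Two SDs below the mean is 33.6 − 63.6 = −30.0, which is impossible for a non-negative quantity and suggests right skew. An adjusted analysis should therefore not rely on ordinary normal-theory standard errors alone.

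**The case against.** The strongest reply is that an unadjusted comparison is valid in a 1:1 randomised trial, contradicts nothing in the article and matches the sample size calculation. A condensed article may also leave model terms to a fuller plan, and the mixed model is already one of the two options. Adjustment has costs too: under the stated missing-data rule, a patient lacking a baseline score would drop out of an adjusted model but not out of the t-test. All of this stands. It limits the point to a better use of data already collected, and it shapes the fix. It does not remove the point, because the article does name an unadjusted primary test and does leave the pain model open.

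Three stronger readings are tempting, and the documents do not support them.

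- A reader might infer that baseline pain is excluded from every analysis. For the primary tests that follows from the methods named. For pain the text is only silent.
- A reader might infer that baseline will enter the ANOVA as a third time level and dilute the group effect. Section 2.4 defines pain outcomes at T6 and T24 only, and nothing places baseline among the repeated measures.
- A reader might infer that adjustment is needed to rescue an underpowered trial. Section 2.7 states a one-sided test, and its 56 per group reproduces. Whether the final test is one-sided or two-sided is a different question.

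**Conclusion.** The point holds as an avoidable loss of precision, plus an open model choice that affects which patients are analysed. It does not make the planned analysis invalid.

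Its size cannot be fixed from the documents. Baseline adjustment is worth 4%, 9% or 25% of the variance at assumed correlations of 0.2, 0.3 or 0.5, and almost nothing at 0.1. The mixed model is worth about 3–8% of the standard error against complete-case ANOVA, assuming 5–10% independently missing at each time and a within-patient correlation of 0.3 to 0.7. This second gain concerns the secondary pain outcomes only and arises only if the ANOVA would otherwise be chosen.

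It would be wrong to conclude that the mixed model settles the missing walking scores. Patients who cannot walk at T6 are not missing at random in any obvious sense, and the mixed model does not fully remove that bias.

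**What to change.** Settle the following in the analysis plan before unblinding.

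1. **Pain.** Delete the ANOVA option. Fit one linear mixed model for rest pain and one for walking pain, with group, time (T6, T24), group-by-time and the matching baseline pain as a covariate, not as a third time level. Report the group contrast at T6 and at T24.
2. **24-h opioid consumption.** Report the mean difference adjusted for baseline pain, with a 95% CI from robust or bootstrap standard errors. State in advance whether this or the unadjusted test carries the primary conclusion; the precision is gained only if it is the adjusted one.
3. **Missing baseline scores.** Keep these patients by simple baseline imputation, for example the overall mean taken without regard to group. Word this as an explicit exception to the no-imputation rule, limited to baseline covariates.
4. **T6 walking pain in patients unable to walk.** State how they enter the walking-pain comparison, and read it beside the reported frequency of inability to walk.

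The cost is a change of wording and slightly more analysis work on data already being collected, one degree of freedom per covariate, and a gain that may be small if the correlations turn out weak.

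### The missing-data rule makes the primary opioid comparison a complete-case analysis, although it is labelled intention-to-treat

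*Protocol article*

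**What the plan says.** All the relevant rules are in the protocol article, mainly in Section 2.8.

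- Analysis principle: "Analyses will follow the intention‐to‐treat principle".
- Missing data, in the next sentence: "Missing data will not be imputed or included in the analyses", "but the frequency and reasons will be reported in the article".
- Primary outcome: the 24-hour total in oral morphine equivalents is formed by "combining hospital‐administered opioid doses from the patient file and self‐reported intake of dispensed morphine tablets".
- Source of the self-reported part: at T24, "patients will be sent an automated text message including a survey link". The same survey collects T24 pain and the Quality of Recovery-15.
- Pain: "Pain intensity will be analyzed with repeated measures ANOVA or linear mixed‐effects models".
- Later detail: changes to the statistical plan will be reported, "with the final detailed plan included in the publication".

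Section 2.5 adds that patients take the morphine tablets themselves after leaving the post-anesthesia care unit, up to a stated oral maximum of 100 mg in the first 24 hours. Section 2.7 sets 56 patients per group and enrols 60, to cover dropouts and variability.

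**The concern.** The primary outcome has two parts with different risks of being missing. Hospital doses are in the patient file. Tablet intake is known only if the patient answers the survey, since the article mentions no tablet count or telephone contact. About one third of these patients go home on the day of surgery (Discussion), so part of the intake takes place out of the staff's sight.

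Without the survey there is no complete total, and the stated rule then takes the patient out. What remains is a comparison of responders. Randomization protects that comparison only if non-response does not distort the two arms differently. It is plausible, though the documents do not show it, that patients with much pain, nausea or sedation at 24 hours answer less often. If that happens to a different extent in the two arms, the primary difference is biased. The information already recorded on the excluded patients would not be used to gauge by how much.

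**Working it through.** **Step 1: which patients leave the analysis.** The total is file doses plus surveyed tablets (Section 2.8). With no survey, the second term is unknown and so is the total. Missing data are neither imputed nor included (Section 2.8), so the patient is not in the primary comparison. The article does not say this in so many words. It follows from the two statements together, and nothing in the article says how a partly observed total is handled.

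**Step 2: the plan's own sample size.** Inputs from Section 2.7: SD 31.8 mg, difference 15 mg, one-sided alpha 0.05, power 0.80.

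n per group = 2 × (1.645 + 0.842)² × 31.8² / 15² = 55.6, rounded up to 56.

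The stated figure is reproduced. Enrolling 60 leaves room for 4 losses per group, 4/60 = 6.7%.

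**Step 3: power when surveys are missing.** Power = Φ(15 / (31.8 × √(2/n)) − 1.645), with n the number left per group. The documents give no rate of missing surveys, so the rates below are assumptions, taken as equal in both arms.

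| Missing | n left per group | Power |
|---|---|---|
| 0% | 60 | 82.6% |
| 6.7% | 56 | 80.3% |
| 10% | 54 | 79.0% |
| 15% | 51 | 76.9% |
| 20% | 48 | 74.7% |

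**Step 4: bias in the group difference.** In one arm, let d be the share missing and k the mean opioid use of non-responders minus that of responders. The full-arm mean is the responder mean plus d × k, so the complete-case mean is too low by d × k. For the difference 20 mL minus 10 mL:

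bias = d10 × k10 − d20 × k20, which is (d10 − d20) × k if k is the same in both arms.

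Both d and k are assumptions.

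- Equal rates and equal k, for example 10% in each arm: (0.10 − 0.10) × k = 0 mg for any k.
- 5% missing with 10 mL and 15% with 20 mL: −0.10 × 10 = −1.0 mg, −0.10 × 15 = −1.5 mg, −0.10 × 30 = −3.0 mg. The sign favours 20 mL.
- 15% with 10 mL and 5% with 20 mL: +1.0, +1.5 and +3.0 mg. The sign goes against 20 mL.

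Against the 15 mg relevant difference, 1 to 3 mg is 1/15 = 7% to 3/15 = 20%. The upper end is demanding: an excess of 30 mg is nearly the whole reference mean of 33.6 mg in Section 2.7.

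**The case against.** The strongest reply is that intention-to-treat often means only that patients are analysed in the arm to which they were randomized, which is compatible with not imputing. Complete-case analysis with reported reasons is also common for a single 24-hour outcome. Patients are blinded (Section 2.3) and must have a smartphone with internet access (Section 2.2), so large differences in response between arms are not to be expected. Much of this stands, and it limits the size of the problem. It does not remove the mismatch between the label and a rule that leaves some randomized patients out.

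A second reply is that a condensed article leaves missing-data detail to the full plan, and that a final plan is announced. The absence of a sensitivity analysis from the article is indeed no fault in itself. But the ban on imputation is stated, and a later plan could bring in all randomized patients through imputation only by reversing it.

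A reader might go further in three ways that the documents do not support.

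- **That T6 pain is thrown away too.** T6 pain is a secondary outcome. The mixed model that Section 2.8 permits keeps a T6 value when T24 is missing. Repeated measures ANOVA with listwise deletion would not, but the choice is open.
- **That nothing would reveal the problem.** The frequency of and reasons for missing data will be reported. This would show unequal or pain-related non-response, though it would not correct for it.
- **That the plan itself allows for 6.7% missing in one arm.** The four extra patients are added to both groups, for dropouts and variability together, not for unanswered surveys in one of them.

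**Conclusion.** The point holds in a limited form. By inference from Section 2.8, the primary analysis is restricted to randomized patients who return the T24 survey, and the intention-to-treat label claims more than the rule delivers. Non-response alone does not bias the difference in means: the product of missing rate and excess use has to differ between arms. Under the assumed 10-point difference in rates and 10 to 30 mg excess, the bias is 1 to 3 mg in either direction. That is unlikely to overturn a clear result but could matter near the 15 mg threshold or near the significance limit. Power stays close to the planned 80% up to about 10% missing and is 74.7% at 20%, on the one-sided test of Section 2.7. The sample size of 56 is correct on its own inputs and is not in question. This is a cheap improvement to the plan, not a defect that invalidates it.

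**What to change.** Amend the missing-data rule in Section 2.8 before unblinding, in three parts.

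1. Name the primary analysis for what it is: patients analysed as randomized, restricted to those with an observed 24-hour total. State how a total with file doses but no survey is handled.
2. Lift the ban on imputation for one pre-specified sensitivity analysis that contains all randomized patients. Keep the recorded hospital opioids as observed and impute only the missing tablet intake, within group, using hospital opioids, baseline pain and T6 pain.
3. Shift the imputed tablet intake up and down by group over a range stated in advance, and report whether the conclusion on the mean difference changes. If the oral maximum in Section 2.5 is kept to, tablet intake lies between 0 and 100 mg, which bounds the range.

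The groups can stay masked throughout, so this fits the blinded analysis in Section 2.3. The cost is a little analysis work. The downside is reliance on an imputation model, which the shifted analyses are there to test. Imputation will recover lost power only as far as the recorded variables predict tablet intake.
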